#### Secondary outcomes analysis

Secondary outcome variables will be analyzed using the same modeling framework used for the primary outcome variable, although the study is not powered to analyze these outcomes or moderation effects on the primary outcome. Dichotomous outcomes will be analyzed using logistic regression. The results will be presented as estimates or odds ratios (with respective 95% confidence intervals [CIs] and *p *values), as appropriate. We will also compare the proportions of treatment responders and full or partial remitters in each group with logistic regression and odds ratio (95% CI). Between-group effect sizes will be estimated using Cohen’s *d*.

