### Participants

#### Eligibility criteria

The inclusion criteria for participation are (1) a primary diagnosis of BDD, based on the 5th edition of the Diagnostic and Statistical Manual of Mental Disorders (DSM-5) [32]; (2) a total BDD symptom severity score ≥24 on the Yale-Brown Obsessive-Compulsive Scale Modified for Body Dysmorphic Disorder, Adolescent version (BDD-YBOCS-A); (3) age between 12 and 17 years; (4) a minimum of one available parent/caregiver able to co-participate and support the adolescent throughout the treatment; and (5) regular access to a computer connected to the Internet and a mobile phone to receive text messages.

The exclusion criteria are (1) previous CBT for BDD for a minimum of five sessions with a qualified therapist within the 12 months prior to the inclusion assessment; (2) simultaneous psychological treatment for BDD or for any psychiatric comorbidity; (3) initiation, change of dosage, or cessation of any selective serotonin reuptake inhibitors (SSRIs) or antipsychotic drugs within the 6 weeks prior to the inclusion assessment; (4) a diagnosis of organic brain disorder, intellectual disability, psychosis, bipolar disorder, eating disorder, severe depression, or alcohol/substance dependence; (5) immediate risk to self or others requiring urgent medical attention or inpatient care, such as suicidality, or repeated self-injurious behaviors; (6) a documented suicide attempt in the last 12 months; (7) adolescent and parent/caregiver not able to read and communicate in Swedish; or (8) having a close relationship to an already included participant (e.g., sibling, cousin), to avoid being randomized into two different arms, with the risk of information “leaking” between the groups.

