#### Secondary outcome measures

Treatment response and full or partial remission rates will be calculated at each follow-up point. Following current consensus in the field [40], treatment response will be defined as a reduction ≥30% on the BDD-YBOCS-A from baseline and full or partial remission will be defined as a total score ≤16 on the BDD-YBOCS-A.

Other secondary clinician-rated outcomes will include the Clinical Global Impressions Scale—Severity (CGI-S) and the Clinical Global Impressions Scale—Improvement (CGI-I), compared with baseline [41], as well as the Children’s Global Assessment Scale (CGAS) to assess global functioning of the young person [42]. All assessors will be trained in the use of the CGI-S, CGI-I, and CGAS and will rate them in addition to the BDD-YBOCS-A.

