### Power analysis

Between-group effect sizes in an RCT comparing face-to-face CBT with an active control in youth with BDD [5] and an RCT comparing ICBT with an active control in adults with BDD [26] were *d* = 1.13 and *d* = 0.94, respectively. Other pediatric ICBT trials similar to ours have reported smaller effect sizes. For example, an ICBT study of adolescent OCD [58] and an ICBT study of adolescent social anxiety disorder [59] reported between-group effect sizes of *d* = 0.69 and *d* = 0.64, respectively. Similarly, an adult BDD trial with an active control condition reported an effect size of *d* = 0.76 [60]. Thus, we have powered our study to be able to detect at least a moderate effect size of *d* = 0.50. A sample size of 128 participants was calculated to be sufficient with a power of 80%, with a 2-tailed *α* = 0.05. An additional 20% of participants will be added to account for potential dropouts. Hence, we aim to recruit a total of 154 participants (77 per group).

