To ascertain whether the intervention is cost-effective, we will calculate an incremental cost-effectiveness ratio, as the ratio between the difference in costs and the difference in QALYs or responders between interventions, for each costing perspective and express them as cost per additional QALY and cost per responder. We will explore uncertainty around the cost and outcome estimates and perform relevant sensitivity analyses.

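### Remission at a fixed score is compared by logistic regression with no baseline severity term, at a modest cost in precision (minor)

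*Protocol article*

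**What the plan says.** Under Secondary outcome measures, "full or partial remission will be defined as a total score ≤16 on the BDD-YBOCS-A". Under Eligibility criteria, entry requires "a total BDD symptom severity score ≥24 on the Yale-Brown Obsessive-Compulsive Scale Modified for Body Dysmorphic Disorder". The Secondary outcomes analysis section says the trial will "compare the proportions of treatment responders and full or partial remitters in each group with logistic regression and odds ratio", with a 95% CI. It lists no covariates for these models and does not rule any out.

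The same section puts secondary outcomes in the modelling framework of the primary outcome. Under Primary outcome analysis, that framework is a linear mixed model in which baseline is one of three time points of the outcome, beside group, site and their interactions. It also says that the study is not powered for secondary outcomes.

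The Statistical analysis section refers to a full statistical and health economic analysis plan (Supplementary File 2). That plan prevails where it differs from the article, and it is to be finalised before the last participant reaches the primary endpoint.

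**The concern.** A fixed cut-off makes remission easier to reach from a low starting score than from a high one. If baseline and follow-up scores correlate, baseline severity therefore predicts remission.

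For the continuous score, the mixed model brings baseline in as a visit. For remission that route is closed, because the entry floor lies above the remission threshold and every participant is a non-remitter at baseline. The article names no replacement.

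If the comparison is run as worded, the remission result is less precise than the collected data allow. In a given trial it also leans towards whichever arm happens to start less severe. At stake is the reading of one secondary outcome, not the primary conclusion.

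**Working it through.** **1. The plan's own figure.** The Power analysis section sizes the trial to "detect at least a moderate effect size of *d* = 0.50" with 80% power and "2-tailed *α* = 0.05". Normal approximation: n per arm = 2 × (1.96 + 0.8416)² / 0.50² = 2 × 7.849 / 0.25 = 62.8, so 63. The t-test version gives 63.77, so 64 per arm and 128 in total, with power 0.801. Adding 20%: 128 × 1.2 = 153.6, so 154. Both stated totals reproduce. The article gives no expected rate or power for remission.

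**2. The fall that remission requires.** Required fall = baseline − 16. Entering at 24: 8 points (8/24 = 33%). Entering at 40: 24 points (24/40 = 60%).

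**3. Why the shared framework cannot supply baseline.** Since 24 > 16, the remission indicator is 0 for everyone at baseline. A baseline visit would carry no information on individual severity, and a logistic model with that visit would run into separation.

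**4. Power for remission.** From the article: d = 0.50, two-sided 0.05, entry at 24 or more, remission at 16 or less, and 64 per arm (the size before the dropout addition). Assumed, because the article gives none: baseline normal with mean 31 and SD 5 truncated to 24–48, follow-up SD 9, control follow-up mean 22 or 25, and baseline-endpoint correlation r. Follow-up score = control mean − 0.50 × 9 × group + 9r × (standardised baseline) + 9√(1 − r²) × (standard normal error), rounded and limited to 0–48. There were 4,000 trials per setting, each with a Wald test from the logistic model.

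Hand check at control mean 22: the control rate is Φ((16.5 − 22)/9) = Φ(−0.611) = 0.271 and the ICBT rate is Φ((16.5 − 17.5)/9) = Φ(−0.111) = 0.456. Simulated at r = 0.2: 0.269 and 0.455. Log odds ratio 0.814, SE 0.377, z = 2.16, so unadjusted power is about Φ(2.16 − 1.96) = 0.58. Simulated: 0.59 to 0.60.

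| r | Control mean 22: unadjusted → adjusted | Control mean 25: unadjusted → adjusted |
|---|---|---|
| 0.2 | 60.0 → 59.7% | 52.9 → 53.6% |
| 0.4 | 60.0 → 63.6% | 53.5 → 56.8% |
| 0.6 | 59.2 → 68.9% | 55.6 → 64.6% |

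The gains are about 0, 3 to 4, and 9 to 10 points. A run with follow-up SD 8 (remission about 43% against 25%, 1,500 trials per setting) gave 58.3 → 60.3% at r = 0.3, 57.7 → 63.1% at 0.5 and 57.6 → 67.6% at 0.6. A further run under assumed SDs gave gains of about 0, 2, 4 and 9 points at r = 0.2, 0.4, 0.5 and 0.6.

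**5. Chance imbalance.** The difference in mean baseline has SD √(2/64) = 0.177 baseline SDs, so it exceeds 0.25 SD in either direction in about 16% of trials. In the step 4 settings, the unadjusted test statistic correlates −0.14 to −0.47 with that difference; after adjustment the correlation is about 0.

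Type I error for remission with no treatment effect (control mean 22; r = 0.2, 0.4, 0.6):
- All trials: 4.8, 4.6, 4.8% unadjusted; 4.9, 5.0, 5.4% adjusted.
- Trials with imbalance above 0.25 SD: 6.1, 6.3, 9.6% unadjusted; 5.5, 5.1, 6.0% adjusted.

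The second row rests on about 0.15 × 4,000 = 600 trials, so its standard error is about √(0.05 × 0.95/600) = 0.9 points. Only the 9.6% is clearly above 5%.

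**6. Odds ratio and absolute difference.** With p1 = OR × p0 / (1 − p0 + OR × p0), an odds ratio of 2.5 gives differences of 18.5, 22.4 and 21.4 points at control rates of 20%, 35% and 50%. The odds ratio alone does not convey the absolute effect.

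**The case against.** The strongest reply is that the missing baseline term is read from silence. The article names the method but gives no covariate list, and covariates of a secondary binary model are commonly left to the analysis plan, which is not shown and takes precedence. This stands in part: a reader might infer that the trial has decided against adjustment, and the article does not say so. What remains is that the wording describes a two-group comparison of proportions, and that the one stated mechanism for using baseline cannot work for remission.

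A second reply is that little depends on it. The study is declared not powered for secondary outcomes, the primary inference uses the continuous score, and the loss is negligible at low correlation. This is fair and keeps the point minor. Being underpowered is still no reason to leave out a covariate that is collected on everyone.

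Two stronger readings are not supported:
- That response suffers in the same way. Response is defined relative to each participant's own baseline, so the fixed cut-off argument does not apply. In the step 4 simulation, adjustment changed its power by between −0.6 and +4.4 points; with follow-up SD 8 the change was at most 1 point.
- That the odds ratio is the wrong input for the cost-effectiveness ratio. The Health economic analysis section already defines that ratio as "the ratio between the difference in costs and the difference in QALYs or responders between interventions", and nothing says the odds ratio feeds it.

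**Conclusion.** The point holds for remission only and is minor. As worded, the comparison omits a predictor that the fixed cut-off makes relevant, and the shared framework cannot bring it in. The cost is about 0 points of power at a correlation of 0.2, 2 to 4 at 0.4, and 9 to 10 at 0.6, with dependence on chance baseline imbalance that grows with the correlation. These sizes rest on assumed means, SDs and correlations, 64 per arm and d = 0.50. A reader might infer that the unadjusted test is invalid; it is not, since randomisation keeps its overall type I error near 5%. The issue is precision and conditional bias in a particular trial. Whether the final analysis is affected depends on the analysis plan.

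**What to change.** Check whether the analysis plan already adjusts remission for baseline severity. If it does not, state there that the logistic model for remission includes baseline BDD-YBOCS-A as a continuous covariate. From the same model, report the standardised (marginal) risk difference with its 95% CI beside the odds ratio.

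The cost is a sentence or two in the analysis plan, with no new data and no change to the sample size. The plan is still to be finalised, and the Trial status section expects the last primary endpoint in March 2028. The one drawback is that the adjusted odds ratio is conditional on baseline and not directly comparable with unadjusted odds ratios from other trials; the marginal risk difference gives readers a figure without that problem.

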#### Long-term follow-up analysis

All trial participants will be naturalistically followed up and assessed up to 6 months after the end of the treatment. Linear mixed-effects models will be implemented for the primary and secondary outcome measures. As for the primary outcome, for each secondary outcome measure, the model will include fixed effects of time (three time points: 1-month follow-up, 3-month follow-up, 6-month follow-up) and site, as well as a time by site interaction, and subject effects as a random intercept factor to account for the variances between and within participants. As above, site will be dropped from the model if its effects are not significant.

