Additionally, CBT for BDD is a highly specialized treatment, often difficult to access due to lack of trained professionals and geographical barriers. A possible solution is to deliver a low-intensity online version of the treatment with minimal remote support from a clinician, similar to a therapist-guided self-help intervention [20]. This approach has the potential to be used in a stepped-care, scalable model of healthcare, making better use of the existing clinical resources [21, 22]. ICBT has a strong evidence base for a wide range of disorders and has been shown to be cost-effective, needing less therapist time per patient than face-to-face CBT [23–25]. A small body of literature also supports the efficacy of ICBT for adults with BDD. A Swedish program, called BDD-NET, was successfully evaluated in an RCT (*N* = 94) where ICBT was compared to supportive therapy [26], with response rates in line with face-to-face CBT and sustained treatment effects up to two years post-treatment [27]. In the USA, an app-based intervention was also successfully evaluated in an RCT for adults with BDD (*N* = 80) [28]. We have recently conducted an uncontrolled feasibility trial (*N* = 20) of an ICBT program for 12-to-17-year-olds with BDD showing that the intervention is feasible, acceptable, and safe [29]. Preliminary efficacy results showed statistically significant BDD symptom severity reductions (*d* = 2.94), with treatment gains that continued to accrue up to the 12-month follow-up [29].

The primary aim of this RCT is to evaluate the clinical efficacy of a previously piloted [29], therapist-guided ICBT program for adolescent BDD versus an active comparator consisting of Internet-delivered relaxation training (IRT) for BDD. Secondary aims include examining the 6-month durability of the treatment effects in a naturalistic follow-up and conducting a health economic evaluation of ICBT for BDD. We hypothesize that ICBT will be superior to IRT in reducing BDD symptom severity, that the effects of ICBT will be durable, and that ICBT will be more cost-effective than IRT.

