### Study design and setting

The study is a multisite, parallel-group, randomized controlled superiority trial for children and adolescents with BDD. Participants will be randomized to either 12 modules of therapist-guided ICBT or 12 modules of therapist-guided IRT for BDD. Participants will be assessed at baseline, mid-treatment, post-treatment, and 1 month, 3 months, and 6 months after the end of the treatment. The primary endpoint is the 1-month follow-up. At the primary endpoint, participants initially assigned to the IRT condition will be offered to cross-over to receive ICBT for BDD. Participants in either group who are still in need of further treatment after ICBT will be referred to their local services or other appropriate services. Participants in both arms will be followed up for 6 additional months after the end of the intervention (those initially randomized to IRT will be followed up regardless of whether they accept the cross-over or not). The 3- and 6-month follow-ups are naturalistic (i.e., uncontrolled). Figure 1 depicts the study design using the Consolidated Standards of Reporting Trials (CONSORT) 2025 [31] flow of participants.

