### Interventions

#### Treatment format and therapist support

Both treatments are delivered over the Internet using BASS, a digital platform provided by the eHealth Core Facility at Karolinska Institutet that is also used as a data collection tool and database for storing the data. Both interventions are therapist-guided and consist of two separate sets of modules, one for the child/adolescent and one for the parent/caregiver, each with separate logins.

Table 1 contains an overview of the content of the interventions. Each intervention consists of 12 modules delivered over a maximum period of 14 weeks. During this time, participants (both the child/adolescent and the parent/caregiver) have regular contact with a therapist in the platform. The therapist will provide brief asynchronous support during the treatment, which includes feedback, answering questions, and sending reminders to complete the next module, if required. Communication during the treatment is possible via text messages in the online platform (resembling e-mail). The therapist usually logs in daily (on workdays, at least every 48 h). There are no specified limits to the therapist’s time. Telephone calls are possible if the participant or the therapist feel that they are needed. The participants are welcome to contact their therapist at any time, who will reply during office hours.

**Table 1 Tab1:** Overview of the treatment modules for both child/adolescent and parents/caregivers in each condition

Module	Internet-delivered cognitive-behavior therapy arm	Internet-delivered relaxation training arm
1	Introduction and information about body dysmorphic disorder	Introduction and information about body dysmorphic disorder
2	Learning more about body dysmorphic disorder and set up treatment goals	Learning more about body dysmorphic disorder
3	What is exposure therapy?	What is anxiety?
4	Starting exposure practice	Starting relaxation practice: deep breathing
5	Focus on response prevention	Relaxation practice: arms, legs, and back
6	How body dysmorphic disorder affects family and school	Relaxation practice: head, jaw, neck, stomach, and chest
7	Body dysmorphic disorder thoughts and attention training	Relaxation practice: whole body
8	Full response prevention	Imagery (cognitive relaxation)
9	Exposure with response prevention practice	Relaxation with and without audio file in different positions
10	Exposure with response prevention practice	Repeating previously practiced relaxation exercises

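### The long-term follow-up model names no treatment group, so read literally its time effect does not estimate the ICBT-specific change that the durability hypothesis needs

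*Protocol article*

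**What the plan says.** The hypothesis, in the Background, concerns one arm: "that the effects of ICBT will be durable". Six-month durability is a named secondary aim.

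The section on long-term follow-up analysis opens with "All trial participants will be naturalistically followed up and assessed up to 6 months after the end of the treatment". It then lists the model terms: "fixed effects of time (three time points: 1-month follow-up, 3-month follow-up, 6-month follow-up) and site, as well as a time by site interaction". The only other term is a random intercept for each participant. Site is dropped if its effects are not significant, which leaves time alone. Treatment group, group by time, crossover status, a restriction to one arm and a separate fit per arm are all absent.

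The primary outcome analysis, by contrast, lists treatment group and its interaction with time among the fixed effects.

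On crossover, the study design section says "At the primary endpoint, participants initially assigned to the IRT condition will be offered to cross-over to receive ICBT for BDD", and that "those initially randomized to IRT will be followed up regardless of whether they accept the cross-over or not". The same section describes the 3- and 6-month visits as naturalistic and uncontrolled.

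**The concern.** Whether ICBT effects last is a question about change after 1 month in people randomised to ICBT. A model with time and site only, fitted to both arms, estimates an average change over two groups in different situations. One group has finished ICBT and may hold, extend or lose its gains. The other has finished relaxation training and is being offered ICBT, so part of it may show a first response to that treatment.

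If crossovers improve, which is what the trial's own hypothesis about ICBT predicts, the averaged change moves towards improvement whatever happens in the ICBT arm. The article plans to put the follow-up data in the main paper, and its Discussion makes implementation in regular care depend on ICBT being shown durable, among other things. The estimate should therefore match the claim.

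**Working it through.** **The plan's own figure.** None exists for the long-term analysis. The only figures used from the power section are 154 participants in total and 77 per group, at 1:1 allocation.

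**Terms side by side.**
- Primary model: time, group, site, all their two-way interactions and the three-way interaction, random intercept.
- Long-term model: time, site, time by site, random intercept.

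The long-term sentence begins by referring back to the primary outcome, but the list that follows is explicit and omits group, so the reference does not restore it.

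**What the time effect estimates if both arms enter.** With equal arms, and assuming IRT participants who do not cross over do not change:

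pooled change = (ICBT change + uptake x crossover change) / 2

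Positive values mean worsening on the BDD-YBOCS-A. None of the input values below is in the documents. They are assumptions for illustration.

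ICBT worsens by 2 points from 1 to 6 months:
- uptake 50%, gain 3: (2 - 1.5)/2 = +0.25
- uptake 50%, gain 5: (2 - 2.5)/2 = -0.25
- uptake 90%, gain 3: (2 - 2.7)/2 = -0.35
- uptake 90%, gain 5: (2 - 4.5)/2 = -1.25

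The ICBT change is +2 in all four rows. The pooled change is exactly zero whenever uptake x gain equals the ICBT worsening, for example 50% uptake with a 4-point gain: (2 - 2)/2 = 0.

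The same uptake and gains with other ICBT courses:
- ICBT unchanged: (0 - 1.5)/2 = -0.75 to (0 - 4.5)/2 = -2.25
- ICBT worsens by 4: (4 - 1.5)/2 = +1.25 to (4 - 4.5)/2 = -0.25

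So the pooled figure misstates the ICBT course even when gains are fully held.

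**Simulation check.** 100 simulated trials of 77 + 77 were run with assumed values: ICBT worsening by 4 points, 75% uptake, crossover gain of 8, between-subject SD 7, residual SD 4, no dropout and no site effect. The formula gives (4 - 6)/2 = -1.0. The mixed model with time only averaged -1.00. Adding group and group by time gave +3.95 for ICBT and -5.96 for IRT, against true values of +4 and -6.

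**Timing.** "Each intervention consists of 12 modules delivered over a maximum period of 14 weeks", with modules opening weekly. If crossover starts promptly at 1 month and visits are counted from the end of randomised treatment:
- 12 to 14 weeks is about 2.8 to 3.2 months, so the course ends at about 3.8 to 4.2 months
- the 3-month visit falls about 8.7 weeks after the offer (2 x 52.18/12), during the course
- the 6-month visit falls about 21.7 weeks after the offer (5 x 52.18/12), after the course has ended

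Under those two conditions, both later visits in the IRT arm carry crossover treatment or its aftermath.

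**The case against.** The strongest reply is that pooling is not stated outright. The opening sentence of the section says who is followed up and assessed, not who enters the model, whereas the primary analysis states its population explicitly. A time-only model is also the natural form for a within-arm analysis of an uncontrolled follow-up. If the sponsor means to fit it per arm, or in the ICBT arm only, the ICBT change is estimable. This stands as a limit on the point: pooling is the literal reading, not a declared intention. It does not remove the point, because the article gives a full term list and no per-arm fit.

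A second reply is that a separate analysis plan exists and prevails where it differs. That plan is not shown and may settle the matter. The terms themselves, however, are fixed in the article rather than left to the plan. If the plan fits by arm, the article's description needs correcting.

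A third reply is that response and remission rates are to be calculated at each follow-up point, and the secondary analysis compares these proportions by group. If that extends to 3 and 6 months, a marked loss of ICBT gains could show there. This reduces the risk of masking but gives no ICBT-specific mean change.

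A fourth reply is that the worsening used above is invented, and that the Background cites pilot gains still accruing at 12 months. That is fair: the figures show that masking is possible, not that it is likely.

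That the visits are uncontrolled explains why there is no randomised contrast after 1 month. It is no reason to merge the arms.

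**Conclusion.** Wrong as written, and a should-fix for a secondary aim. Taken literally, the model does not identify the change in the ICBT arm on which the durability hypothesis rests. With an assumed ICBT worsening of 2 points, the pooled estimate lies between +0.25 and -1.25 over 50-90% uptake and 3-5 point crossover gains, with non-crossovers taken as unchanged. The primary comparison at 1 month and the sample size are untouched.

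Two stronger readings go beyond the documents. A reader might infer that durability would be reported as met while gains are being lost. The article gives no durability criterion and nowhere says that a null time effect will count as durability, so this could happen but is not planned. A reader might also take it as settled that the 3-month visit falls during crossover ICBT. No crossover start date is given, and the study design section does not say which intervention's end starts the 6-month clock for crossovers. The dates under Trial status suggest the end of randomised treatment, so the timing is plausible rather than stated.

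**What to change.** State the analysis set and the estimate. Either fit the durability model in participants randomised to ICBT only, or keep all participants and add original group and group by time. In both cases report the ICBT mean change from 1 to 6 months with its 95% CI as the durability result. Describe the IRT arm separately by crossover status, with time also shown from the start of crossover ICBT. If group by time is used, add that the between-arm difference after 1 month is not a controlled comparison of ICBT with IRT.

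The cost is wording only: no visit, treatment or sample size changes. An ICBT-only fit uses about 77 rather than 154 participants. With the same residual variance and dropout, the interval is about sqrt(154/77) = 1.41 times as wide. Recruitment stood at 100 of 154 in the Trial status section, and the analysis plan stays open until before the last participant reaches the primary endpoint, so the change can still be prespecified.
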